## Abstract

**Background:**

Primary care professionals (PCPs) are responsible for identifying eligibility and supporting patient decisions for a wide range of recommended screenings. However, the number of recommendations (42 for adults in France), complex eligibility criteria, limited consultation time, and competing priorities hinder their systematic delivery. Clinical decision support systems (CDSSs) with patient decision aids may help structure prevention-focused consultations and support shared decision-making, but their feasibility and acceptability in routine primary care remain uncertain. As part of the Aide aux Dépistages Recommandés (ADER) research program, we developed Lianeli, a CDSS designed to provide individualized, patient-centered support for all nationally recommended screenings.

**Objective:**

ADER-Faisabilité (ADER-F) is a study with the primary objective of assessing the feasibility of implementing Lianeli in routine primary care by estimating the proportion of patients for whom the CDSS is used to completion. Secondary objectives are to (1) quantitatively and qualitatively describe implementation feasibility, (2) describe organizational adjustments and interprofessional work related to the intervention, (3) explore the association between interprofessional use of Lianeli, health literacy, social deprivation, and feasibility, and (4 and 5) estimate the proportion of eligible, overdue or never screened patients who engage in organized or opportunistic cancer screening, respectively.

**Methods:**

ADER-F is a noncomparative, multicenter feasibility study with a mixed methods design conducted in primary care centers in the Auvergne-Rhône-Alpes region in France. We plan to recruit 210 adult patients from 21 general practitioners (GPs) across 17 sites. During routine consultations, eligible patients will be invited to complete a self-administered digital health questionnaire in Lianeli, which applies guideline-based algorithms to identify recommended screenings. Within 60 days, patients will attend a dedicated screening consultation during which the GP will validate the patient’s responses, discuss benefits and harms of each screening using shared decision-making, and update the patient’s screening pathway. Quantitative data will include Lianeli metadata, sociodemographic characteristics, health literacy, social deprivation, implementation feasibility measures (Guideline Implementation with Decision Support [GUIDES]–based questionnaires), and usability measures (French version of the System Usability Scale [F-SUS]). Semistructured interviews with patients and PCPs will be analyzed thematically and integrated with quantitative findings in a convergent metasynthesis.

**Results:**

The ADER-F study was funded in 2023. Following ethics approval in October 2025 and French National Commission on Data Protection authorization in February 2026, recruitment started in March 2026, with a planned 2-month inclusion period and an overall study duration of 6 months. The results are expected to be published in 2027.

**Conclusions:**

ADER-F will provide evidence on the feasibility and acceptability of a patient-centered CDSS to support recommended screenings in French primary care. The findings will identify determinants of successful implementation, guide possible developments of the Lianeli software and care pathways, and determine whether a subsequent effectiveness study is justified.

**Trial Registration:**

ClinicalTrials.gov NCT07270926; https://clinicaltrials.gov/study/NCT07270926

**International Registered Report Identifier (IRRID):**

PRR1-10.2196/89922

## Introduction

### Background

Primary care professionals (PCPs), particularly general practitioners (GPs), play a central role in identifying patients eligible for recommended screenings, informing them of potential benefits and harms, and supporting shared decision-making [1,2]. In France, the French National Authority for Health (Haute Autorité de Santé; HAS) produces recommendations for organized screenings (eg, breast, colorectal, and cervical cancer) and opportunistic screenings (eg, hypertension), as well as other preventive interventions (eg, behavioral counseling about tobacco). The number of these recommendations (n=42 for adults) and eligibility criteria make it challenging to systematically identify all eligible patients in everyday practice and to properly inform patients about these screenings [3].

In addition to this complexity, several barriers limit the delivery of preventive care, including screenings, in primary care settings [4]. The lack of time during consultations and the need to prioritize acute or chronic issues over prevention are frequently reported by GPs [5,6]. In France, the mean GP consultation time was 17 minutes in 2014 [7]. Patients who consult infrequently are particularly at risk of missing opportunities for prevention [8]. Patients also lack information on screening options, which can impede informed decisions [9]. Inadequate health literacy and social deprivation are additional sources of inequity in the uptake of recommended screenings [10,11].

Clinical decision support systems (CDSSs) are designed to provide patient-specific assessments or recommendations to support clinical decision-making [12]. For prevention and screening, they could match patient characteristics with guideline-based algorithms to identify eligibility, communicate benefits and risks with patient decision aids, and help structure shared decision-making discussions [13]. CDSSs can improve PCPs’ adherence to guidelines [14]. Patient decision aids may reduce decisional conflict and support self-efficacy [15]. According to PCPs, the successful implementation of CDSSs in real-world settings depends on usability, integration into workflows, and alignment with professional expectations [16].

The Aide aux Dépistages Recommandés (ADER) research program supports the design, implementation, and evaluation of a complex intervention centered on the use of a patient-centered CDSS called Lianeli [17]. Lianeli uses a self-administered health questionnaire to collect individual information (eligibility criteria) and then applies guideline-based algorithms from the HAS national guidelines to identify eligibility for recommended screenings. The tool generates tailored information about screening eligibility, including explanations of risk stratification, potential benefits and harms, and provides a summary that can be integrated into the electronic health record (EHR). This information can be discussed during a dedicated screening consultation. Such a dedicated consultation was introduced in 2024 by the French National Health Insurance Fund to promote preventive care [18].

## Methods

### Study Design

ADER-F is a prospective, regional, multicenter, noncomparative feasibility study conducted in routine primary care. It corresponds to step 2 in the development and evaluation of a complex health intervention [19]. The study applies mixed methods to integrate quantitative and qualitative data in a convergent metasynthesis [20]. The study draws on the GUIDES theoretical framework, a reference for assessing determinants of successful implementation of guideline-based CDSSs [21]. This framework comprises 16 criteria, evenly distributed across 4 domains: enabling context, appropriate content, effective system, and effective implementation. Textbox 1 presents key characteristics of the study design. The full description of GUIDES indicators evaluated in the present study is available in Multimedia Appendix 1. Figure 1 presents the design of the study, including the anticipated participant flow and the data collected at each step.

**Figure 1 figure1:**
[figure not shown]
Design of the Aide aux Dépistages Recommandés-Faisabilité (ADER-F) study: participant flow and corresponding data collection. EHR: electronic health record; EPICES: Evaluation of Precarity and Inequalities in Health Examination Centres; F-SUS: French version of the System Usability Scale; GP: general practitioner; GUIDES: Guideline Implementation with Decision Support; HLS-EU16: European Health Literacy Survey Questionnaire-16; PCP: primary care professional.

Key characteristics of the ADER-F (Aide aux Dépistages Recommandés-Faisabilité) feasibility study.
**Study design**
Noncomparative, multicenter, regional feasibility study with a mixed methods design
**Study setting**
Primary care practices in the Auvergne-Rhône-Alpes region, France
**Population**
Patients aged 18-74 years consulting participating general practitioners (GPs)
**Intervention**
Use of the Lianeli clinical decision support system (CDSS) and a dedicated screening consultation
**Primary objective**
To estimate the proportion of patients for whom Lianeli is used completely in routine care
**Secondary objectives**
Implementation feasibility (Guideline Implementation with Decision Support [GUIDES] domains), organizational impact, effect of interprofessional use, health literacy, and social deprivation on the primary outcome, and potential impact on screening participation
**Planned sample size**
21 GPs and at least 210 patients (≈10 patients per GP)
**Planned study duration**
6 months (2-month inclusion period plus follow-up and qualitative interviews)
**Primary outcome**
Proportion of patients with complete use of Lianeli (patient questionnaire completed, GP validation of the questionnaire, and screening consultation within 60 days)
**Data collection**
Lianeli metadata, patient and primary care professional (PCP) questionnaires, semistructured interviews
**Analysis**
Descriptive and exploratory quantitative analyses, thematic qualitative analysis, and convergent mixed methods metasynthesis guided by the GUIDES framework

This protocol is reported in accordance with the Consensus Reporting Items for Studies in Primary Care (CRISP) 2023 statement [22]. As an interventional study, this protocol is reported in accordance with the applicable items of the SPIRIT (Standard Protocol Items: Recommendations for Interventional Trials) 2013 statement: the completed checklist is provided in Multimedia Appendix 2 [23]. The mixed methods components will be reported following the Good Reporting of a Mixed Methods Study framework, and the qualitative components will follow the Consolidated Criteria for Reporting Qualitative Research (COREQ) [24,25].

### Setting

The study will be conducted in 17 primary care centers (participating sites) involving 21 GPs in the Auvergne-Rhône-Alpes region of France. Participating sites will include solo GP practices, one community health care center, and multiprofessional group practices. They may involve other PCPs in the delivery of the intervention (team-based practices), depending on the local organization, as long as a GP conducts both the inclusion and dedicated screening consultations. Before patient recruitment, all participating GPs will receive a standardized online training session on the use of the Lianeli CDSS and on the study procedures, delivered by the research team. There will be no restriction on concomitant care during the study.

### Eligibility Criteria

Table 1 describes the patient and PCP eligibility criteria.

**Table 1 table1:** Study eligibility criteria.

Population and category			Criteria
**Patients**			
	Inclusion	Age 18-74 years Consulting a participating GP^a^ in the Auvergne-Rhône–Alpes region Covered by the French national health insurance Able to understand and write in French sufficiently to complete the questionnaire (with PCP^b^ support if needed) Having provided written informed consent to participate in the study	
	Noninclusion	Pregnant or breastfeeding woman Under legal protection Presenting with a psychiatric disorder or psychiatric symptoms associated with impaired judgment, as assessed by the investigator Participating in another clinical study that could interfere with the ADER-F^c^ study	
	Exclusion	Withdrawal of consent	
**GPs**			
	Inclusion	GPs working in primary care settings in the Auvergne-Rhône-Alpes region	
**Other PCPs**			
	Inclusion	Health professionals (eg, nurses and medical assistants) working in participating sites	

^a^GP: general practitioner.

^b^PCP: primary care professional.

^c^ADER-F: Aide aux Dépistages Recommandés-Faisabilité.

### Recruitment and Informed Consent

#### PCPs and Patient Recruitment

We recruited PCPs through university-affiliated teaching practices via email.

Patients will be recruited during routine consultations, as part of usual care, with participating GPs (visit 1). The GP will present the study and verify eligibility criteria. Patients who agree to participate will receive oral and written information describing the objectives, procedures, potential benefits and risks, data confidentiality, and their rights (including the right to withdraw at any time without consequences for their care). Written informed consent will be obtained before any data collection specific to the research.

#### Recruitment for Qualitative Interviews

Qualitative semistructured interviews will be conducted by a health psychologist with a purposive sample of volunteer patients and PCPs to assess the feasibility of implementing the Lianeli system. Their agreement to participate in the interviews will be documented in the written consent form. Participation in these interviews is contingent upon obtaining written authorization for audio recording and the use of the recorded data. Nonsampled patients or PCPs will be notified by email or mail. We will aim for maximum variation in sex, age, and health literacy for patients, and in sex, age, and diversity in roles for PCPs. Up to 24 interviews per group are planned, with early termination possible upon data saturation. Among PCPs (GPs and other professionals), semistructured interviews will be performed at the end of the patient recruitment phase in each center.

### The Lianeli CDSS

Lianeli is a CDSS that provides individualized assessment of eligibility for recommended screenings based on the French HAS guidelines. The system is designed to collect relevant patient information (eg, age, sex, personal and family history, and risk behaviors) via a self-administered digital health questionnaire, and to automatically apply the French HAS national screening recommendations to this information to determine which screenings are recommended for each patient. To support shared decision-making during a dedicated screening consultation, Lianeli then provides factual, patient-friendly information on the practical considerations of each recommended screening and, when available, on the benefits and harms of screening options. Finally, the system generates a structured summary of screening eligibility and decision outcomes, designed for inclusion in the patient’s EHR at the end of the consultation. As Lianeli currently operates as a standalone web-based application, transfer to the EHR requires a manual step.

The Lianeli CDSS was developed by a scientific interdisciplinary committee from a systematic review of French screening recommendations [3] and then tested internally against clinical vignettes and real cases for reliability. The system adopts a patient-centered approach, empowering patients to complete the questionnaire independently (or with assistance) and equipping them with the information needed to prepare for the discussion with their GP. This integrated approach distinguishes Lianeli from existing tools, which often focus on a single pathology or do not support shared decision-making.

### Timeline

The ADER-F study is structured into 4 main steps (Figure 1). At least 210 patients will be included, and 21 GPs will be recruited over a 2-month period, with a total study duration of 6 months. The expected participation duration is between 1 day and 3 months for patients (extended by up to 1 additional month for those participating in qualitative interviews) and 6 months for PCPs.

#### Step 1 (Visit 1): Inclusion Consultation (Day 1)

The GP identifies an eligible patient, presents the study, and obtains informed written consent. A time for reflection will be systematically proposed. After visit 1, the patient is invited to complete the self-administered digital health questionnaire within the Lianeli, either in the waiting room with a tablet computer, with assistance from a PCP if needed (according to local organization), or at home within 28 days.

#### Step 2 (Visit 2): Dedicated Screening Consultation (Day 1 to Day 60)

Within 60 days of inclusion, the patient attends a dedicated consultation focused on screening. The GP reviews, completes, if needed, and validates the health questionnaire within Lianeli. The GP engages in a discussion with the patient regarding the eligibility and personal relevance of recommended screenings, weighing benefits against potential harms. A summary of screening eligibility and shared decision-making outcomes is integrated into the EHR.

#### Step 3: Quantitative Survey

After visit 2, patients complete a survey based on the GUIDES patient checklist (Multimedia Appendix 3). After achieving their inclusion targets, PCPs complete a similar GUIDES-based implementation survey (Multimedia Appendix 4). These GUIDES-based questionnaires combine validated instruments (French version of the System Usability Scale [F-SUS]) with items constructed for the study and have not undergone psychometric validation [26].

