### Outcomes

#### Overview

In the ADER-F study, feasibility refers to the extent to which the intervention can be delivered as intended in routine primary care; it is assessed primarily through the proportion of patients with complete use of Lianeli (primary outcome) and through objective CDSS use and data quality metrics (Table 2). Acceptability refers to the extent to which patients and PCPs consider the intervention appropriate, satisfactory, and usable; it is assessed through the GUIDES-based surveys, the F-SUS usability score, and the qualitative interviews.

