#### Primary Outcome

The primary outcome is the proportion of included patients for whom the Lianeli CDSS is used completely. Complete use is defined as meeting all 3 of the following criteria: the patient validates completion of the Lianeli self-administered health questionnaire (criterion 1), the GP checks data quality and validates the patient’s responses (criterion 2), and the dedicated screening consultation is conducted within 60 days after the inclusion consultation (criterion 3). This outcome is binary at the patient level (complete vs incomplete use).

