**SO1: quantitative feasibility criteria**				
	Percentage of Lianeli health questionnaires started and completed, percentage validated by GPs^a^, number of dedicated consultations, missing data rates before vs after GP review of the health questionnaire, percentage of documented previous screening tests, and patient error rate regarding past examinations	Lianeli CDSS^b^ (automatically recorded metadata)	Continuously recorded from visit 1 to visit 2 (day 1 to day 60)	Descriptive statistics
	GUIDES^c^ patient survey (22 items, including the F-SUS^d^; Multimedia Appendix 3)	eCRF^e^ or paper-based survey, with the help of research assistants if needed	After visit 2, no later than 90 days after inclusion	Descriptive statistics
	GUIDES PCP^f^ survey (22 items, including the F-SUS) (Multimedia Appendix 4)	eCRF or paper-based survey	At the end of the inclusion period	Descriptive statistics

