### Sample Size

As a feasibility study, ADER-F is not designed to detect clinical effects on practice or patient outcomes but to estimate feasibility and acceptability parameters. No formal hypothesis-testing power calculation was performed. Instead, a minimum sample size of 210 patients (approximately 10 patients per GP, across 21 GPs) was chosen to allow precise estimation of the primary feasibility outcome.

A sample size of 210 patients ensures that the SE of the estimated proportion of complete Lianeli use remains below 4%, irrespective of the observed rate. Consequently, observing a complete use rate of at least 77% will allow us to conclude that the true participation rate exceeds 70% (with a 2-sided type I error of 5%).

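### The patient GUIDES/F-SUS survey is tied to visit 2, so patients who start Lianeli but never attend visit 2 give no survey or usability score

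*Protocol article*

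**What the plan says.** The section Step 3: Quantitative Survey states: "After visit 2, patients complete a survey based on the GUIDES patient checklist (Multimedia Appendix 3"). The SO1 block of Table 2 describes the instrument as "GUIDES^c^ patient survey (22 items, including the F-SUS^d^; Multimedia Appendix 3") and times it "After visit 2, no later than 90 days after inclusion". Neither place gives an alternative time for a patient who has no visit 2.

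The Outcomes overview rests acceptability on three sources: "it is assessed through the GUIDES-based surveys, the F-SUS usability score, and the qualitative interviews". It does not restrict acceptability to patients who attended the consultation.

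Under Primary Outcome, visit 2 is itself one of the three conditions for complete use: "the dedicated screening consultation is conducted within 60 days after the inclusion consultation (criterion 3").

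The Statistical Analysis section counts every included patient in the primary analysis. For categorical variables it computes percentages on non-missing answers. It calls missing data informative, but neither imputes nor adjusts for them.

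On the interviews, Recruitment for Qualitative Interviews says "We will aim for maximum variation in sex, age, and health literacy for patients" and caps each group at 24. Step 4 adds that patients who leave early may be interviewed.

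**The concern.** A patient enters the survey by passing one of the steps that define feasibility. Someone who opened Lianeli, struggled with the health questionnaire and did not return has direct experience of the tool but is scheduled for no rating. Because percentages leave out missing answers and nothing is adjusted, the reported GUIDES percentages and the F-SUS mean will be figures for visit 2 attenders, with nothing in the plan that labels them so.

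This matters because acceptability is one of the two properties the study sets out to describe. The Implications section also expects the GUIDES indicators to show what helps and what hinders use of the software before an effectiveness trial is designed. The Strengths and Weaknesses section names incentives, research-assistant support, a Hawthorne effect and volunteer self-selection as limitations, but not this selection.

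**Working it through.** **Inputs from the protocol article.** Planned size: "a minimum sample size of 210 patients (approximately 10 patients per GP, across 21 GPs"). Feasibility threshold 70%, two-sided exact binomial test at 5%. Observed rate said to be sufficient: 77%. Stated precision: the SE "remains below 4%, irrespective of the observed rate". The article gives no figure for the survey, no expected visit 2 attendance and no ratings from non-attenders.

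**Step 1: the plan's own figures.** SE = √(p(1−p)/210). The maximum, at p = 0.5, is √(0.25/210) = 3.45%. At 70% it is 3.16% and at 77% it is 2.90%, so the statement of below 4% holds. Exact test against 70%:

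- 160/210 (76.2%): p = 0.0504
- 161/210 (76.7%): p = 0.035
- 162/210 (77.1%): p = 0.024, Clopper-Pearson lower limit 70.9%

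The 77% figure is right to the nearest percent.

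**Step 2: how many could be unsurveyed.** Every complete user has had visit 2, so patients without it are a subset of the incomplete users.

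- 70% complete use: 210 × 0.30 = 63
- 77% complete use: 210 × 0.23 = 48.3, about 48

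These are ceilings. An incomplete user may have attended visit 2 but failed another criterion. A visit 2 after day 60 fails the 60-day criterion but can still be followed by the survey before day 90.

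**Step 3: what that could do to an estimate.** Let c be the share reaching visit 2. Then

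bias = (1−c) × (mean in attenders − mean in non-attenders).

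Both c and the difference are assumptions here. Taking 80% acceptability in attenders and 20–60% in non-attenders:

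| c | surveyed / not | value in all included | bias (points) | worst-case bounds | SE in those surveyed (points) |
|---|---|---|---|---|---|
| 0.70 | 147 / 63 | 62–74% | 6–18 | 56–86% | 3.3 |
| 0.77 | 162 / 48 | 66–75% | 5–14 | 62–85% | 3.1 |
| 0.85 | 178 / 32 | 71–77% | 3–9 | 68–83% | 3.0 |

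The worst-case bounds are c × 0.80 and c × 0.80 + (1−c). For example, at c = 0.70 they are 0.56 and 0.86.

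For an F-SUS mean 10–30 points lower in non-attenders, the bias is 0.30 × 10 to 0.30 × 30 = 3–9 points at c = 0.70, 2.3–6.9 at 0.77 and 1.5–4.5 at 0.85. A usability score has meaning only for people who opened Lianeli. If all attenders opened it, the weight (1−c) among openers is no larger than shown, so the F-SUS figures are ceilings for each assumed difference.

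The bias is zero if both groups rate alike, and negative if non-attenders rate higher.

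**Step 4: do other parts of the plan supply the missing scores?**

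- *Telephone completion* (Data Collection and Management) is offered after 14 days without a response. It follows up a survey already due and does not move the visit 2 anchor.
- *The call within 7 working days of inclusion* collects baseline data and helps with connection. It is not described as collecting the GUIDES survey.
- *Metadata* record questionnaires started, completed and validated, and consultations held. They show where patients stop, but not how they rate the tool.
- *Interviews* can include early withdrawals. They are optional, capped at 24, sampled on sex, age and health literacy but not on completion status, and give no estimate.

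**The case against.** The strongest reply is that these patients are seen by other routes. Interviews are one of the three acceptability sources and admit early withdrawals, metadata locate the stage of drop-out, research assistants telephone every patient soon after inclusion, and professionals have their own survey and interviews. This stands. A reader might infer that the barriers met by non-completers go wholly unobserved, and the document does not support that. What is missing is a survey score from these patients and any assurance that the interviews will reach them.

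Second, limiting a usability scale to users is defensible, since a patient who never opened Lianeli has nothing to rate. This also stands. The gap that matters most is the group who started Lianeli and did not reach visit 2.

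Third, a reader might infer that the results are certainly biased upward, or by a stated amount. The document gives no reasons for non-attendance, which could be scheduling or illness, and no ratings from non-attenders. The upward direction is a reasonable expectation, and the sizes above are illustrations. Nor are 63 and 48 expected counts, because 70% is a threshold and 77% a decision value.

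Fourth, the survey is secondary and descriptive, with no decision rule attached. That limits the consequence but does not remove it.

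Finally, the article is condensed, and the full protocol may arrange contact with non-attenders. But the article does not leave the timing open: it states it twice, the same way each time.

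**Conclusion.** The point holds for the quantitative patient survey. As written, GUIDES and F-SUS results apply to patients who reach visit 2, a component of the feasibility outcome, and the plan neither says so nor provides a survey for the rest. At 70–77% complete use, at most 63–48 of 210 patients (30–23%) are unsurveyed for this reason. Under the assumed contrasts at attendance of 70–77%, acceptability would be overstated by about 5–18 points, against a sampling SE of about 3 points. Those contrasts are not in the document, and the true size cannot be derived from it. The primary outcome and its 70% test are unaffected. This is a cheap improvement to a secondary measure and does not threaten the main conclusion.

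**What to change.** - **Trigger.** Send the survey at visit 2 or, if none has occurred, at day 60, to all included patients who have not withdrawn consent. Keep the 90-day limit and the telephone fallback.
- **Content.** Give the F-SUS only to patients who opened Lianeli. Mark consultation items as not applicable for non-attenders. Ask patients who never opened Lianeli only the GUIDES items that apply to them.
- **Reporting.** Present results by completion status and overall, with the response rate out of all included patients.
- **Interviews.** Add completion status to the purposive sampling frame.

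If the trigger cannot be changed, state that the survey and F-SUS results apply only to visit 2 attenders and list this as a limitation.

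The cost is up to about 48–63 extra contacts at 77–70% complete use, by research assistants already in place, and probably lower acceptability figures. Patients who withdraw consent would still be missed.
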